### Instruments

The SPIRIT diagram (Table 1) below summarizes the schedule of enrollment, assessments, and visits across the study.

**Table 1 Tab1:** Study SPIRIT diagram

TIMEPOINT	STUDY PERIOD		
	ENROLLMENT	VISIT SCHEDULE	
	Day 0	Week 4	Week 8
ENROLLMENT			
Eligibility screening checklist	X		
Informed consent	X		
Allocation (L+/L-)	X		
ASSESSMENTS AND MEASURES			
Demographics and characteristics	X		
Wound assessment and medical health history	X	X	
VEINES-QOL/Sym - 26 item			
PROMIS Cognitive Function 6a	X	X	X
PROMIS Global Health Scale - 10 item	X	X	X
PROMIS Anxiety 6a	X	X	X
PROMIS Fatigue 6a	X	X	X
PROMIS Pain Interference 6b	X	X	X
PROMIS Sleep Disturbance 6a	X	X	X
Katz Activities of Daily Living - 6 item	X	X	X
Mini-nutritional status - 7 item	X	X	X
UCLA Loneliness Scale - 20 item	X	X	X
Medical Outcomes Social Support Survey - 19 item	X	X	X
Patient Health Questionnaire - 9 item	X	X	X
The Stigma Scale: Body Image and the Skin - 8 item	X	X	X
Blood Sample: RNA for deep sequencing analysis*	X	X	X

**Chemotaxic factors:* CCL2/JE/MCP-, CCL3/MIP-1 alpha, CCL4/MIP-1 beta, Granzyme B, CCL5/RANTES, CCL11/Eotaxin, CCL19/MIP-3 Beta, CCL20/MIP-3 alpha, CX3CL1/Fractalkine, PD-L1/B7-H1, CXCL1/GRO alpha/KC/CINC-1, CXCL2/GRO, and CXCL10

**Immune regulators:* IL-3, IL-4, IL-5, IL-6, IL-7, IL-8/CXCL8, IL-10, IL-12 p70, IFN-alpha IL-13, IFN-beta IL-15, IFN-gamma IL-17/IL-17A, IL-1 alpha/IL-1F1, IL-17E/IL-25 CD40 Ligand/TNFSF5, IL-1 beta/IL-1F2, IL-33, IL-1ra/IL-1F3, and IL-2

**Vascular damage:* VCAM, ICAM, CRP, MMP-1, MMP-3, and MMP-

**Growth factors:* PDGF-AB/BB, TGF-alpha, EGF, TNF-alpha, FGF basic/FGF2 Flt-3 Ligand TRAIL, G-CSF, GM-CSF, VEGF, and PDGF-AA

#### Aim 1. Stressors and symptoms measures

In our previous trials, we tested the feasibility of the battery of instruments which took approximately 45 min to complete and found this was acceptable to our patients. However we are mindful of response burden and the time commitment for completing questionnaires and having blood specimens obtained. At the 3 data collection periods during regular wound clinic visits, participants can opt to answer questionnaires via assistance from study personnel in paper form or electronically on a tablet. Participants in both groups will receive the same battery of instruments. Psychometrically-sound measures include PROMIS® and other measures of loneliness, social isolation, depression, anxiety, stigma, cognition, and function. Data on wound type and size, wound age, and treatment will be recorded from the electronic health record. In the event that a participant expresses psychological distress when responding to psychological questionnaires (e.g., depression scale), our study wound physician will be contacted. We developed a plan for referral of depressed or suicidal participants.

#### Aim 2: blood draws for genomics analyses

Patient blood samples will be drawn by study personnel via venipuncture directly into PAXgene RNA tubes which inhibit RNA degradation and allow for purification of RNA for subsequent sequencing analyses. All blood samples will be drawn during the clinic visit, placed in the transport bag, immediately delivered directly to the MUSC laboratory at room temperature, and and slowly frozen to − 20 °C prior to processing, shipping, and analysis. RNA from patient samples will be sequenced in a blinded fashion in batches. We will attempt to schedule patients for clinic visits between 9 and 11 am to reduce the influence of diurnal variations.

### Feasibility and process monitoring

We will observe 10% of data collection procedures including questionnaires and specimen collection at least monthly. The team will track other study procedures through review of consenting logs, noting any problems encountered during interviewing and specimen analysis, participant burden of completing questionnaires/time taken, and document other barriers such as transportation that arise during data collection.

### Data analyses

Univariate descriptive statistics and frequency distributions will be calculated as appropriate for all variables. Inflammatory profiles, loneliness, psychosocial variables, and physical and functional variables will be obtained at baseline (V1), month 1 (V2) and month 2 (V3). Preliminary analyses will explore patterns of missing data for all outcome variables. We will also explore differences in demographic and other variables such as age (60–74, ≥75 years), sex, chronic illnesses, cognition, health status, functional activity, nutritional status, length of time to heal (healing trajectory), and wound treatment type across the 3 time points. All statistical analyses will be conducted using SAS Statistical Software Version 9.4 (Copyright© 2016 by SAS Institute Inc., Cary, NC, USA).

#### Analyses for aim 1

The primary variables for aim 1 are social isolation and social support (psychosocial stressors) and fatigue, pain, depression, anxiety, sleep disturbance, reduced QOL (symptoms). To examine differences in and variability of psychosocial stressors and symptoms over time between the L+ and L- groups, we will compare the longitudinal profile of the psychosocial stressors and symptoms (in individual models) between the groups over the 3-month study period using mixed effects models (MEM) analyses. These analyses will estimate the average change in the dependent variable within each group (L+ vs. L-) and individual change in variables for participants. MEM analyses allow for missing data, measurement of study subjects at different time points during the study, and time varying covariates. MEM can also take into account the effect of clustering, e.g., correlation of repeated measurements within one subject. The psychosocial stressor or symptom will be used as the dependent variable with group (L+ vs. L-), time, and time-by-group interaction as primary independent variables. The GLMM analysis approach allows for time-varying variables; we will also report separately whether and how many patients switch from L+ to L- or vice versa. Nutritional status, functional activity, and wound treatment will be investigated during secondary analyses through inclusion as covariables in the longitudinal models (individually). Further, frequency distributions of adverse events and serious adverse events will be obtained. Proportions within categories of adverse eventsand serious adverse events for the L+/L- groups will be compared via chi-square analyses.

#### Analyses for aim 2

All RNA sequencing will be performed at the UCLA Social Genomics Core Lab. RNA will be extracted from PAXgene tubes (Qiagen RNeasy), tested for suitable mass and integrity, and converted to cDNA libraries using a high-efficiency enzyme system (Lexogen QantSeq 3′ FWD). Normalized cDNA libraries will be sequenced using an Illumin HiSeq 4000 instrument, targeting > 10 million reads per sample. Reads will be aligned to the reference human transcriptome and quantified as gene transcripts per million total mapped reads using the STAR aligner. Transcript abundance data will be log2 transformed for analysis by linear statistical models quantifying differential gene expression as a function of key predictors (e.g., loneliness wound healing) while controlling for potential confounders, particularly age, sex, race/ethnicity, BMI, smoking history, and heavey alcohol consumption history. The CTRA will be measured by a pre-specified 53-gene composite score used in previous social genomics studies, [48, 49] including 19 gene transcripts involved in inflammation (i.e., *IL1B, IL6, IL8, TNF*), 34 gene transcript involved in innate antiviral responses (*IFNB, IFI-, MX-,* and *OAS-*family genes). Scores will be composed by z-score standardizing expression of each gene and summing the resulting values after sign-reversing the antiviral genes to reflect their inverse contribution to the CTRA profile.

#### Analyses for aim 3

The goal of aim 3 is to explore whether age and sex/psychological stressors and symptoms indicate potential moderation/mediation of the effect of loneliness on the biomarker profile over the study period. The composite score of the biomarker expression values will be used as the dependent variable for this analysis. Subsequently, to compensate for the limited sample size of this exploratory analysis, a bootstrapping procedure that resamples the data with replacement will be employed to provide more accurate estimates of variability (95% CIs). The analysis will involve a comparison of the composite score between L+ and L- using MEM as described above. Moderators will be explored through inclusion of an interaction term in the model, for example, age-by-loneliness. Potential mediators will be explored individually using MEM. Exploratory analyses will follow the modified procedure suggested by MacKinnon, Fairchild & Fritz [48] of the causal steps approach developed by Baron & Kenny [50].

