#### Sample size considerations

With 28 participants per group we will have 80% power to detect an effect size of 0.6 standardized units effect size between the 2 groups, assuming 2 post-baseline time points; intra-class correlation no greater than 0.4; level of significance [α] = 0.05, two-tailed. Assuming standard deviation (sd) = 2, this translates into a raw effect size (difference in change scores) of 1.2. If the pooled sd is 5 units, the standardized effect size is equivalent to a raw detectable difference in change scores between the groups of 4.5 raw scale units. We will enroll 10 males and 10 females prior in each group so that we can complete thorough data analysis for outcome comparisons by sex. If necessary we will over enroll to achieve 28 participant per group at V3. The distribution of patients at one of our main wound centers is 60.0% male, 40.0% female; 60.0% African American, and 40.0% White with mean age 70 years.

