We recognize the small sample size may not allow for detecting statistically significant differences; however, as the focus of the exploratory aim is to generate hypotheses rather than to confirm, we will be able to establish preliminary relationship profiles among the psychosocial stressors and symptom variables. In addition, we will investigate whether there is an indication for clinically relevant differences that support further focused exploration in future studies.

We acknowledge generalizability of the anticipated results is limited in this small exploratory study and anticipate, in a future trial, we will have an adequately powered study and a greater diversity (Latinx) of participants. To this end, we will develop study materials, for example, in Spanish to reflect the diversity of the population.

The projected racial and ethnic composition of the participant sample is a concern given the established differences in gene expression among and between these groups; it is unlikely that the least frequent groups (e.g., Hispanic) can be properly evaluated in the proposed analyses, impacting on rigor. We agree and acknowledge the concern about the differences in gene expression among various ethnic/racial groups; for this small exploratory trial, we are focused on fidelity to our PNI model. Though it is not the primary aim of this observational study to determine ethnic differences, we have included age, sex, and race and ethnicity as individual person factors based soundly in the PNI model and these variables will be included and accounted for in preliminary analyses.

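### Aim 1 has eight primary variables and two primary between-group terms per model, but one power figure and no settled deciding contrast; the stated 80% fits a three-visit group average, not the change-score difference it names

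*Protocol article*

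**What the plan says.** The Aim 1 analysis section opens with the list of outcomes: "The primary variables for aim 1 are social isolation and social support (psychosocial stressors) and fatigue, pain, depression, anxiety, sleep disturbance, reduced QOL (symptoms". That is eight variables, all of equal rank. On method it says "we will compare the longitudinal profile of the psychosocial stressors and symptoms (in individual models) between the groups", using mixed models "with group (L+ vs. L-), time, and time-by-group interaction as primary independent variables".

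Sample size considerations gives one power statement: "With 28 participants per group we will have 80% power to detect an effect size of 0.6 standardized units", "assuming 2 post-baseline time points; intra-class correlation no greater than 0.4", "level of significance [α] = 0.05, two-tailed". It names no outcome. It describes the detectable quantity for an SD of 2 thus: "this translates into a raw effect size (difference in change scores) of 1.2".

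The wording of Aim 1 in the Background asks something simpler: whether stressors and symptoms differ between lonely and non-lonely patients. Only Aim 3 carries the word exploratory in its heading. The Discussion, on the small sample, says "as the focus of the exploratory aim is to generate hypotheses rather than to confirm". The same section and the Conclusion also describe the study as a whole as exploratory.

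**The concern.** Three places in the protocol point to three different quantities: a difference in level between groups (the aim), a difference in profile over time (the analysis section), and a difference in change scores (the power statement). The group term and the time-by-group term can disagree for the same variable, and eight variables can disagree with each other. Nothing in the protocol says which result answers Aim 1.

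Two things are at stake. The 80% may be read as applying to a contrast for which the study has clearly less power. And up to sixteen nominal p-values share the label primary, so one that falls below 0.05 could later be presented as the primary result.

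**Working it through.** **Inputs.** From Sample size considerations: 28 per group, 0.6 SD, two-tailed 0.05, ICC at most 0.4, two post-baseline visits. From the Aim 1 analysis section: eight variables, three visits, two between-group terms per model. My assumptions: compound symmetry, 0.6 expressed in SDs of a single measurement, no dropout. (The same paragraph also gives 4.5 units at an SD of 5, which implies 0.9 SD. That is a separate matter; the check uses 0.6.)

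**Step 1: which contrast gives the stated 80%?** For each contrast the variance per participant is f × SD², the standard error is √(f × 2/28), and power comes from the t distribution with 54 df. The n per group for 80% is by normal approximation.

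- Group difference averaged over three visits: f = (1 + 2×0.4)/3 = 0.60; SE 0.207; 0.6/0.207 = 2.90; power 81%; n = 27.
- Group difference in the mean of the two post-baseline visits: f = (1 + 0.4)/2 = 0.70; SE 0.224; ratio 2.68; power 75%; n = 31.
- Change from baseline to the post-baseline mean: f = 0.70 + 1 − 2×0.4 = 0.90; SE 0.254; ratio 2.37; power 64%; n = 40.
- Change from baseline to one visit: f = 2(1 − 0.4) = 1.20; SE 0.293; ratio 2.05; power 52%; n = 53.
- Post-baseline mean adjusted for baseline as a covariate: f = 0.70 − 0.4² = 0.54; SE 0.196; ratio 3.06; power 85%; n = 24. The described model lists no baseline covariate.

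The first contrast reproduces the plan's figure. The upper bound on the ICC points the same way. For the three-visit average, f = (1 + 2ρ)/3 rises with ρ, so an upper bound is the conservative choice. For the change to the post-baseline mean, f = 1.5(1 − ρ) falls as ρ rises, so an ICC below 0.4 would push power below 64%.

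**Step 2: chance of at least one nominal p below 0.05 if every null is true.** With independent outcomes this is 1 − 0.95^8 = 0.337 for eight tests and 1 − 0.95^16 = 0.560 for sixteen. The documents give no correlation between outcomes, so I simulated equicorrelated two-sided z tests (400,000 draws) over a range, treating the group and time-by-group sets as independent of each other:

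| Correlation | 8 tests | 16 tests |
|---|---|---|
| 0 | 34% | 56% |
| 0.3 | 30% | 51% |
| 0.5 | 25% | 44% |
| 0.7 | 19% | 34% |
| 0.8 | 16% | 29% |

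A correlation of −0.5 between the two terms lowers the sixteen-test range only to 27–53%.

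**Step 3: cost of adjusting over eight variables on the three-visit average.** This uses the normal approximation, correlation 0.5, and four or eight true effects of 0.6 SD. Unadjusted power per variable is 0.83 on this scale (0.81 by t). Benjamini-Hochberg at 5% gives 0.70 and 0.78. Holm gives 0.60 and 0.68. Values by t are a few points lower. With four true effects, the chance of at least one false positive under Benjamini-Hochberg is about 0.07, because it controls the false discovery rate and not family-wise error.

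**The case against.** The strongest reply is that this is an exploratory study and says so. The Conclusion applies that label to a project covering stressors and symptoms, which are Aim 1's variables. The Discussion concedes that the sample may be too small for statistical significance and promises only preliminary relationships among those variables. That stands and lowers the weight of the point. It does not settle it: the Discussion sentence ties hypothesis generation to the exploratory aim, the Demographics section applies the same description only to moderation analyses, and Aim 1 keeps primary variables and a powered 0.05 test.

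A multiplicity rule may also sit in a full protocol or analysis plan that is not shown. So its absence from the article is not itself the finding. The finding is what the article does fix: eight primaries, two primary terms, and a power figure whose contrast does not match its arithmetic.

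A reader might infer three stronger things that the document does not support:

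- That a promised 5% family-wise error is broken. No such promise is made; 0.05 appears only as the level in the power statement.
- That sixteen deciding tests are declared. The phrase about primary independent variables lists model terms, time among them. Sixteen is the number available, not a stated decision rule.
- That the false-positive risk has one known value, such as 25% or 44%. Those figures need a correlation of 0.5, which is not in the document.

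Finally, the all-null case is unlikely for some group effects. The Discussion reports that loneliness correlates with depression, quality of life and social support. Setting those three aside leaves five group tests, with 13–23% over correlations of 0.8 down to 0 if null. The cited correlations say nothing about the eight time-by-group tests, which alone carry 16–34%.

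**Conclusion.** The point holds as a matter of unresolved specification. Under compound symmetry with ICC 0.4, the stated 80% agrees with a time-averaged group difference (81%) and disagrees with the unadjusted change-score contrasts the power statement appears to name (64% and 52%). The power applies to one variable at an unadjusted level, not to the set of eight. The 16–34% and 29–56% figures show what unadjusted testing would allow if every null held and any nominal p below 0.05 were taken as an answer. They rest on an assumed correlation and on a global null that is doubtful for part of the group effect. It should be corrected, but given the exploratory framing it does not undermine the study.

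**What to change.** **Analyses for aim 1:** name one deciding contrast per variable. The L+ versus L- difference averaged over the three visits fits the aim's wording and the stated 80%. Make time-by-group secondary and descriptive.

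**Sample size considerations:** say that the power is per variable, unadjusted, for that contrast, and drop the reference to change scores. If change over time is the real target, keep that wording and restate the power for it instead.

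**Then choose one of two routes:**

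- State explicitly that Aim 1 is hypothesis-generating, report all eight estimates with 95% confidence intervals, and make no significance claim. The cost is a softer claim.
- Adjust over the eight variables on the one contrast: Holm if family-wise error is to be controlled, Benjamini-Hochberg if only the false discovery rate is. The cost is per-variable power falling from about 0.83 to 0.70–0.78 (Benjamini-Hochberg) or 0.60–0.68 (Holm), on the assumptions in Step 3.

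Either route changes wording in two paragraphs and needs no further participants or data.

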Examine whether psychosocial stressors (i.e., social isolation, social support) and symptoms (i.e., fatigue, pain, depression, anxiety, sleep disturbance, reduced QOL) differ between (L+) and (L-) patients with CVLUs using well-validated questionnaires.

### Aim 2

Characterize a biomarker (chemotaxic factors, growth factors, vascular damage and immune regulators) profile common to loneliness and CLVU using well-established RNA sequencing and PCR methods for whole blood samples. We will start the analysis using a 1.8-fold change in gene expression, either positive or negative, to generate a composition score to assess the effect of loneliness and stressors on biomarkers.

### Exploratory aim 3

Explore whether age and sex/psychological stressors and symptoms indicate potential moderation/mediation of the effect of loneliness on the biomarker profile over the study period.

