Previous research in social genomics has linked adverse social conditions to increased expression of pro-inflammatory genes in correlational human studies, in experimental animal and human models showing causal effects, and in cellular model systems dissecting the specific molecular signaling pathways involved [39, 43]. Loneliness in particular has been repeatedly linked to up-regulated expression of pro-inflammatory genes (i.e., *IL1B, IL6, IL8, TNF*), and down-regulated expression of genes involved in innate antiviral responses (*IFNB, IFIs, MX, OAS*) [18, 60–66]. This recurring pattern appears to reflect the activation of CTRA in myeloid-lineage immune cells [39, 67]. Our in-depth review of the literature guided the selection of these genes and is based on the best available data. We believe the novelty is in the application of the gene analysis to a population that suffers with wounds. However, the impact of this biomarker profile on chronic wound healing remains unstudied.

We have identified several challenges to our study including relevance of selected biomarkers, models to assess healing, sample size, generalizability of results, and racial/ethnic composition. Increased expression of inflammatory markers is associated with a variety of factors such as older age, multiple chronic conditions (obesity, diabetes), pain, smoking, lower socioeconomic status, and poor functional status [68–70]. We recognize the majority of individuals with CVLUs is generally older (≥60 years of age), has high functional impairment, poor quality of life, and multiple chronic conditions. However it is not known whether there is a distinct profile in patients with chronic wounds and in particular those with loneliness. We will account for these co-variates in our analyses.

Currently there is no assessment mechanism available to predict healing that includes an inflammatory biomarker or psychosocial variables such as loneliness and social isolation. If relationships are indicated among our study variables (and confirmed subsequently), these factors could be added to currently available disease-specific risk factor models to predict non-healing in wound populations. The M.A.I.D. score, predominantly used in wound care, was created out of 4 clinically-defined parameters to estimate long-term clinical outcomes [71]. However, there are no psychosocial, physical or biological components in this score, thus it lacks full scope risk factors for accurate prediction.

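### The 53-gene CTRA score is read in unseparated whole blood with no white-cell composition term named, so a group difference in cell mix could create, mask or reverse an L+/L- difference

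*Protocol article*

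**What the plan says.** Aim 2 (Background) will characterise the biomarker profile "using well-established RNA sequencing and PCR methods for whole blood samples". The section on blood draws for Aim 2 states: "Patient blood samples will be drawn by study personnel via venipuncture directly into PAXgene RNA tubes which inhibit RNA degradation". No step that separates cells is described. Table 1 lists one blood item at day 0, week 4 and week 8, "Blood Sample: RNA for deep sequencing analysis", and no blood count or differential.

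Under Analyses for aim 2, transcript abundance is scaled to total mapped reads, log2 transformed and modelled while "controlling for potential confounders, particularly age, sex, race/ethnicity, BMI, smoking history, and heavey alcohol consumption history". The CTRA score sums gene z-scores over "19 gene transcripts involved in inflammation" and 34 antiviral transcripts, the latter with sign reversed. Under Analyses for aim 3, the composite score is the dependent variable of a mixed model comparing L+ with L-.

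The Discussion lists correlates of inflammation (age, chronic conditions, pain, smoking, socioeconomic and functional status) and says "We will account for these co-variates in our analyses". On the origin of the signal it says: "This recurring pattern appears to reflect the activation of CTRA in myeloid-lineage immune cells". The Background expects the composite to be up-regulated in lonely participants.

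**The concern.** A whole-blood transcript level is an average over all circulating cells, scaled to total RNA. It rises if cells express more of the gene, or if the cells that express it make up a larger share of the sample. The article's reading, up-regulation and activation in one lineage, is a statement about expression within cells. The specimen and the named covariates cannot separate that from a change in cell mix.

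This matters in this population. Infection is not an exclusion, and the section on wound healing trajectory lists infection and osteomyelitis among the features of Grade 3 ulcers, so a plausible cause of white-cell shifts can differ between participants. An imbalance between groups could be reported as a loneliness-related molecular mechanism. Equally, a real difference could be hidden.

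**Working it through.** The article gives no figure on this point to reproduce. The check asks how far a cell-mix difference could move the score with no change in any cell.

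**Inputs from the article:** 19 inflammatory and 34 antiviral genes, z-scored, antiviral sign reversed (Analyses for aim 2); design effect 0.6 SD with 28 per group, two post-baseline points, intra-class correlation up to 0.4, two-sided 5% (Sample size considerations); 1.8-fold starting threshold (Aim 2).

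**Assumptions (not in the article):** the inflammatory genes are expressed in myeloid cells; myeloid share is 66% v 60%, or 69% v 60%; gene SD is 0.4 to 0.6 log2 units; mean correlation of signed z-scores, rho, is 0.1 to 0.3.

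1. Change in a myeloid transcript from cell mix alone: log2(0.66/0.60) = 0.138; log2(0.69/0.60) = 0.202.
2. Score SD = sqrt(53 + 53 x 52 x rho) = 18.1 at rho 0.1 and 29.7 at rho 0.3.
3. Shift in SD = (19 - 34k) x log2 ratio / gene SD / score SD. Here k is the antiviral genes' log2 rise as a fraction of the inflammatory genes' rise. Each range below pairs gene SD 0.6 and score SD 29.7 with gene SD 0.4 and score SD 18.1.

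| Antiviral genes | Net genes | 66% v 60% | 69% v 60% |
|---|---|---|---|
| do not move (k = 0) | 19 | +0.15 to +0.36 | +0.22 to +0.53 |
| rise half as much (k = 0.5) | 2 | +0.02 to +0.04 | not computed |
| rise equally (k = 1) | -15 | -0.12 to -0.29 | -0.17 to -0.42 |

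For example, 19 x 0.138 / 0.4 / 18.1 = 0.36, and -15 x 0.138 / 0.4 / 18.1 = -0.29 (-0.284 with unrounded inputs).

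4. A second parametrisation also allows antiviral genes to fall with myeloid share. Let d be the group difference in myeloid share in SDs, and ri and ra the correlations of inflammatory and antiviral genes with that share. The shift is d(19ri - 34ra) / SD(score). With d = 0.5, ri 0.2 to 0.6, and residual within-block correlation 0.1 (inflammatory) and 0.1 or 0.4 (antiviral):

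| ra | False shift (SD) | Probability of rejecting at 5% |
|---|---|---|
| -0.3 | +0.27 to +0.43 | 22 to 48% |
| 0 | +0.08 to +0.32 | 7 to 30% |
| +0.3 | -0.21 to +0.05 | 5 to 16% |

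The rejection probabilities use 28 per group and variance factor (1 + 0.4)/2 = 0.7, for a comparison of the groups' average level.

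5. Against the 1.8-fold threshold: 0.66/0.60 = 1.10 and 0.69/0.60 = 1.15, both far below it. A gene-by-gene screen at 1.8-fold is therefore little exposed to a modest shift in a majority fraction. The summed composite is what is exposed.

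**The case against.** A reader might infer that the plan makes no adjustment for cell mix, and that a small myeloid shift would be mistaken for activation. Neither is supported. The confounder list opens with *particularly*, so it is not exhaustive, and this is a condensed article; the accurate statement is that no such term is named. The article gives no myeloid shares and no gene loadings. A positive shift follows only if the antiviral genes stay put or fall; if they rise with myeloid share the shift cancels or reverses. A six-point difference may not be small either: if the between-person SD were 10 points (an assumption), it would be 0.6 SD of myeloid share.

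Other handling counts too. Age is a named confounder, chemotherapy and steroids are exclusions, draws are aimed at a fixed morning window, and changes in wound grade and treatment are to be accounted for. That reduces confounding by infection, but grade is a clinical description of the ulcer. It does not measure cell mix and cannot separate mix from expression per cell.

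The 0.6 SD in the sample-size section is framed as a difference in change scores. A stable difference in composition cancels from change, so 0.6 SD serves here only as a yardstick. The exposure remains for average group differences, and for time-by-group terms if composition changes differently over the visits.

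The project is exploratory, the myeloid sentence summarises earlier research in hedged terms, and cell mix may itself lie on the path from loneliness to inflammation. The planned model is therefore not wrong as a total association. What stands is narrower: that model alone does not support a reading in terms of activation within cells.

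**Conclusion.** The concern holds in limited form. Specimen, quantification and named covariates leave cell composition and expression per cell inseparable in the CTRA score, while the article interprets the score as up-regulation linked to myeloid activation. A difference in white-cell mix could create, mask or reverse an L+/L- difference. Under the assumed 66% v 60%, the effect runs from about -0.29 to +0.36 SD as the antiviral genes go from rising equally to not moving; if they fall with myeloid share, it would lie above that range. These sizes rest on assumed shares, gene SDs and correlations. The article settles neither size nor direction, so no claim that bias will occur, or which way it will run, is justified.

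**What to change.** For each Aim 2 and Aim 3 CTRA model, pre-specify a sensitivity version that adds a small number of white-cell composition terms from the same draw. One option is two or three principal components of lineage-marker transcripts in the RNA data already planned, using markers outside the 53-gene score. Report it beside the planned model, which stays the total association. If the L+/L- estimate does not persist after adjustment, word any claim of myeloid activation or up-regulation cautiously.

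No new sample or visit is needed. The cost is analysis wording, a few extra parameters and a wider interval in the second model. With 56 participants, several confounders already named and markers that may be collinear with the score, the widening may not be trivial. Marker transcripts also mix cell number with expression per cell, so they are an imperfect proxy for counts. The adjusted result is a sensitivity analysis, not a clean estimate per cell.
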